### Participants and Recruitment

The enrollment of participants in this study was based on specific inclusion criteria. Individuals aged ≥17 years who were newly enlisted members of the National Guard and had been assigned a ship date to complete BCT during the study period were eligible for participation. Exclusion criteria included a history of prior military service or any previous experience with BCT.

To recruit participants, a consecutive approach was used within designated National Guard Recruitment Sustainment Program (RSP) units across the state until the target sample was reached. The research team recruited participants between April 2019 and October 2021 using briefing presentations held during drill events at military posts. The relevant Army National Guard command provided the research team with a list of all potentially eligible military service members. During the briefings, interested individuals were provided with a study packet, which included a consent or assent letter, a “Help Us Keep in Touch” locator form, a “What to Expect Next” card illustrating the study design in layperson’s terms, and a randomly generated unique study ID number. Throughout the recruitment process, detailed documentation was maintained. This included recording the total number of eligible military service members approached as well as the number of participants enrolled, those who refused to participate, and those found to be ineligible based on the inclusion and exclusion criteria.

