### Statistical Methods

Aim 1 will characterize adaptation among young military recruits over the first 2 years of service. Consistent with a hierarchical concept of the structure of resilience, we will use latent growth mixture modeling to identify the latent trajectories of adaptation and its indicators. We will apply latent growth mixture modeling at the level of internalizing symptoms, externalizing problems, and social-occupational functioning as well as an overall model that simultaneously embeds all 3 domains into a model of adaptive functioning. We hypothesize that at least three trajectories (one showing resilient adaptive functioning or low pathology and the other two showing new-onset and chronic distress) will emerge for each domain assessed (internalizing symptoms, externalizing problems, social-occupational functioning, and global adaptive functioning).

Note that all remaining analyses for aims 2 and 3 will be conducted on the trajectory class membership data for each of these 4 domain outcomes to test for the specificity of resilience mechanisms***.***

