Aim 2 will identify the promotive factors and protective processes contributing to individual variations in adaptation. We will apply structural equation modeling and Bayesian network analysis to detect and identify the latent constructs and the dependency structure between different domains. We will also examine the effects of protective and vulnerability factors on membership in different trajectory classes. We propose to investigate this in 2 complementary ways. First, in our structural equation modeling, we will augment the measurement submodels of the most parsimonious latent growth structural mixture models accepted in aim 1 with the indicators of protective and vulnerability measurements (Tables 1 and 2) and evaluate the change in the relationships (coefficients) that indicators have with the latent trajectories. We will treat potential predictors as moderators or mediators, depending on their hypothesized role in the model, and we will test their contribution to the model by change in model fit indices using the Akaike information criteria (AIC), the Bayesian information criteria (BIC), root mean squared error (RMSE), and goodness-of-fit (G^2^) also known as the likelihood ratio test. Second, the trajectory class membership assignment in aim 1 will be used as dependent variables (resilient vs nonresilient or distressed trajectories), and protective and vulnerability factors will be used as predictors in random intercept multinomial logistic mixed models that will provide a quantitative picture of the unique contribution of these measures. We hypothesize that the risk factors listed in Tables 1 and 2 will predict membership in nonresilient or distressed trajectory classes, whereas protective or promotive factors will predict membership in the resilient or nondistressed trajectory classes. All analyses will be estimated within the propensity classes that adjust for any possible lack of imbalance and will be performed on both complete cases and 5 imputed data sets.

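### Regressions on assigned trajectory class make no allowance for classification error, so predictor effects shrink and intervals undercover unless the classes separate well

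*Protocol article*

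**What the plan says.** All references are to the protocol article.

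- **Outcome.** Under Statistical Methods, aim 1 finds trajectory classes by latent growth mixture modeling and expects at least three per domain. The section then says that "all remaining analyses for aims 2 and 3 will be conducted on the trajectory class membership data for each of these 4 domain outcomes".
- **Aim 2, first approach.** Protective and vulnerability indicators are added to the mixture models accepted in aim 1.
- **Aim 2, second approach.** Here "the trajectory class membership assignment in aim 1 will be used as dependent variables (resilient vs nonresilient or distressed trajectories", and the protective and vulnerability factors "will be used as predictors in random intercept multinomial logistic mixed models that will provide a quantitative picture" of what each measure contributes.
- **Aim 3.** Brain and behavioral responses, with their moderation by other factors, serve as predictors of class membership.
- **Adjustment.** "All analyses will be estimated within the propensity classes that adjust for any possible lack of imbalance".
- **Recruitment.** Under Participants and Recruitment, "a consecutive approach was used within designated National Guard Recruitment Sustainment Program (RSP) units across the state".

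No posterior weighting, pseudo-class draw or bias-adjusted method is stated for the second aim 2 approach or for aim 3. The five imputed data sets deal with missing data, not with uncertainty about class.

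**The concern.** A mixture model gives each person a probability of belonging to each class. Assigning the person to one class and treating that class as observed discards the uncertainty. Some members of the resilient class are then counted as distressed and the reverse, which dilutes the association between a predictor and the class it truly affects. The standard error takes no account of the error in the outcome, so the interval sits in the wrong place and covers the truth too seldom.

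The second aim 2 approach is the one meant to quantify the separate contribution of each factor, and aim 3 has no joint model beside it. A real protective factor could therefore look weaker than it is, to a degree that differs between the four domains only because their classes separate differently. That would blur the comparison of domains by which the plan means to test the specificity of resilience mechanisms.

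Two other parts of the same specification are unclear: the level at which the random intercept applies, and what the propensity is a propensity for.

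**Working it through.** **1. The plan's own figure.** The power statement gives 0.909 at n=780 with 5 df, null RMSEA 0.05 and α=.05. With noncentrality (n−1)·df·RMSEA², the null value is 779×5×0.0025=9.74. An alternative RMSEA of 0.10, which the text does not state, gives 779×5×0.01=38.95 and power 0.909. The recruitment figure also agrees: 780/0.65=1200. This calculation does not cover the class-membership regression, but it supplies the n=780 used below.

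**2. Effect of using assigned class.** The document gives no class shares, effect sizes or separation, so these are assumed.

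- Simulation A: 400 runs, n=780, three classes at 70/15/15%, five waves, intraclass correlation 0.4, odds ratio 1.5 per SD, so true slope ln(1.5)=0.405.
- Simulation B: 250 runs per level of separation, n=780, classes at 75/12.5/12.5%, true slope 0.50 per SD.

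Both compute posterior probabilities at the true mixture parameters, assign each person to the most probable class, and fit a multinomial logit to that class and to the true class. Shrinkage is 1 − (mean slope on assigned class)/(true slope). For example, 1−0.283/0.405=30% and 1−0.32/0.50=36%.

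| Entropy | Simulation | True slope | Slopes on assigned class | Shrinkage | 95% CI coverage |
|---|---|---|---|---|---|
| 0.45 | A | 0.405 | 0.219, 0.209 | 46-48% | 62-67% |
| 0.61 | A | 0.405 | 0.299, 0.283 | 26-30% | 78-84% |
| 0.62 | B | 0.50 | 0.32 to 0.33 | 34-36% | 69% |
| 0.76 | A | 0.405 | 0.355, 0.336 | 12-17% | 90-91% |
| 0.76 | B | 0.50 | 0.38 to 0.42 | 16-24% | 84-86% |
| 0.83 | B | 0.50 | 0.41 to 0.45 | 10-18% | 88-94% |
| 0.87 | A | 0.405 | 0.377, 0.366 | 7-10% | 91-96% |
| 0.94 | A | 0.405 | 0.396, 0.393 | 2-3% | 95-96% |

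Regression on the true class gives 0.40-0.42 with coverage 92-97% in A, and about 0.50 with 93-98% in B, so the loss comes from the assignment. The Monte Carlo standard error of a coverage near 95% is √(0.95×0.05/400)=1.1 points in A and √(0.95×0.05/250)=1.4 points in B; differences of two or three points are noise. At entropy 0.61 a true odds ratio of 1.5 is read as about exp(0.283)=1.33 to exp(0.299)=1.35.

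**3. Random intercept.** Each person has one class per domain. A check used a binary outcome, one per person, with the standard deviation σ of a person-level intercept held at fixed values. The negative log-likelihood per 780 people moves only from 466.259 (σ=0) to 466.276 (σ=3), while the fitted slope rises from 0.397 to 0.832. The data cannot choose among these values, so a person-level intercept within one domain is not identified. Its effect would be to inflate the slope, not to shrink it.

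**4. Propensity classes.** No arithmetic applies. Survey Data Collection Procedures makes exposure to BCT a condition of continued follow-up, so BCT cannot be the contrast. Statistical Methods names no other. Elsewhere propensity appears only as one imputation method, under Handling of Missing Data.

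**The case against.** **The joint model already covers this.** The first aim 2 approach places predictors inside the mixture model and so carries class uncertainty. That stands, and the point does not apply there. It does not reach the second approach or aim 3.

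**The size is unknown.** This also stands. With well-separated classes the loss is negligible. But separation is known only after fitting, and the stated method is sound only if it turns out high.

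**An article may leave the detail to the full plan.** This would answer mere silence. Here the article does state the method: the assignment is the dependent variable.

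**The simulations do not represent aim 3.** This stands in part. The laboratory predictors exist for 123 people, chosen to enrich for risk. Standard errors there would be roughly √(780/123)=2.5 times larger, so a bias of the same size would harm coverage less. The dilution mechanism is the same, but the coverage figures should not be carried over.

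**Stronger readings that a reader might infer.** The documents do not support these:

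- *Every log odds ratio moves toward zero.* With three classes this need not hold. In a check with 200,000 people and known mixture parameters, a predictor that truly affected only one distressed class showed a slope of about 0.02-0.04, in place of 0, for the other (entropy 0.60-0.91).
- *The random intercept is at person level and RSP units are ignored.* No grouping unit is named. RSP unit, or the four domains within a person if modelled jointly, would fit the wording. A design effect for ignored clustering would rest on assumed unit sizes and correlations, and on an omission that the text does not state.
- *No propensity can be defined.* None is defined, which is different. Enrollment before or after the pandemic outbreak, selection into the laboratory substudy, and survey response are all possible contrasts. Claims that strata would be too thin need an assumed number of strata and separate fits in each.

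**Conclusion.** The concern holds for the second aim 2 approach and for the aim 3 regressions that predict class membership. Both use an estimated class as an observed outcome with no stated allowance for classification error. For predictors that act on the distressed classes, the loss is roughly a quarter to a third of the log odds ratio at entropy near 0.6, about an eighth to a quarter at 0.76, and negligible at 0.94, with undercoverage to match at n=780. These sizes rest on assumed class shares, effects and separation, and on mixture parameters taken as known; estimating them would add uncertainty not counted here.

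The grouping unit and the propensity classes are secondary clarifications. A reader might take all three features together as the cause of attenuated effects and short intervals, but only the use of assigned class leads there.

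**What to change.** 1. For the second aim 2 approach and for aim 3, replace regression on assigned class with a bias-adjusted three-step multinomial regression (BCH or ML) or a one-step mixture regression.
2. Report entropy and the classification-error table for each of the four domain models.
3. Name the grouping unit of the random intercept, for example RSP unit. A person-level intercept with one class per domain should not be used.
4. State what contrast the propensity classes model, or remove the phrase and adjust directly for named baseline covariates.

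The cost is analysis wording, standard software, a little more analysis work and somewhat wider intervals. No data collection changes. The three-step correction is safe whether separation turns out good or poor, so it can be fixed before the class models are seen.

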### Handling of Missing Data

Every effort will be made to maximize the completion of data and responding across waves in the longitudinal survey (aims 1 and 2). However, the data collected at each wave will be subject to various random missingness. At the end of each wave, the mechanism of missingness for each measured variable will be assessed, and an imputation model appropriate to that variable (predictor, response, or adjustor covariate) will be identified. Appropriate imputation methods based on variable characteristics (eg, linear regression for continuous variables, multinomial logit models for categorical models, and propensity matching based on multiple predictors) will be used. After selecting a relevant model and, more importantly, deciding on the predictors of missingness, 5 imputed data sets will be constructed for each wave. The relevant analyses will then be based on the combined inferences derived from these 5 imputed data sets.

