### Context and Setting

This study aims to investigate mental health and adaptive functioning among young military recruits before and immediately after BCT and beyond, offering a unique opportunity to study resilience in response to a well-defined, naturally occurring, and uniform military stressor. BCT is a mandatory, intensive, and 10-week training course that all military recruits must successfully complete. The training environment is highly structured and characterized by low personal autonomy, with strict discipline enforced by drill instructors [28]. One distinctive aspect of BCT is the deliberate introduction of numerous stressors into the training environment, designed to prepare recruits for the challenges they will face in future military life [29]. These challenges include prolonged separation from family and friends, dramatic changes in the living environment, extreme physical demands, mental challenges, and simulated combat. This process is believed to foster unit cohesion and cultivate a strong sense of mental and physical toughness known as the *warrior ethos*. Previous research has shown that BCT has positive effects on cognitive performance, mood, and physical fitness [30-34], and it is associated with increased unit cohesion over time, which, in turn, leads to reduced psychological distress and improvements in tolerating training stressors [35].

Although most military recruits successfully adapt to the challenges of BCT, some recruits experience it as highly stressful. A considerable percentage (approximately 20%) of National Guard recruits fail to complete BCT [36]. This suggests that although BCT is a uniform stressor experienced by all recruits, its impact and perceived stressfulness vary among individuals. A study of Swiss Armed Forces recruits participating in a 21-week BCT course found that higher perceived stress at the beginning of the training was associated with greater mental distress and poorer military performance at later stages [37]. Previous studies focusing solely on BCT completers have overlooked valuable data from a significant minority of individuals who exhibit reduced resilience.

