### Administrative Data

The study team will work with the local National Guard to extract administrative data capturing sociodemographic and service-related variables (ie, Armed Forces Qualification Test score, training dates, and military discharge). Administrative data from military records will be deidentified and matched by participant ID.

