### Sample Size and Power Analysis

Sample size was calculated based on the primary objective of the study (aims 1 and 2) using structural equation models of various hypothesized structures (nested and longitudinal). This demand resulted in a sample size that could provide sufficient power to test such hypotheses across varying df. Control of root mean square error of approximation (RMSEA) was the criteria used for our sample size and power calculations. According to MacCallum and colleagues [81], RMSEAs of 0.01, 0.05, and 0.08 indicate excellent, good, and mediocre fit, respectively. Table 4 presents the required sample sizes and the corresponding powers for df=2 and df≥5, assuming a null RMSEA of 0.05 and an α of .05. Assuming a retention rate of 65% to reach an effective sample size of 780, we needed to recruit 1200 participants. Note that for n=780, structural equation models with df≥5 would have an expected power of at least 0.909. The column for df=2 demonstrates that for df smaller than 5, the power for our feasible sample size drops below conventional 0.80.

**Table 4 table4:** Power estimates (chi-squared test for root mean square error of approximation=0.05).

Sample size	Estimate (*df*)	Estimate (*df*)
700	0.567 (2)	0.878 (5)
800	0.619 (2)	0.916 (5)
1000	0.707 (2)	0.961 (5)
1200	0.776 (2)	0.982 (5)

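### Imputation is specified wave by wave under random missingness, although the primary outcome is a mixture of trajectories over all five waves

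*Protocol article*

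**What the plan says.** Under Handling of Missing Data (aims 1 and 2), the article starts from the premise that "the data collected at each wave will be subject to various random missingness". When a wave ends, the mechanism is assessed and an imputation model is identified for each measured variable. Predictors of missingness are then to be decided; none is named. Next, "5 imputed data sets will be constructed for each wave", and the analyses rest on inferences combined over the five sets.

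The Outcomes section makes trajectories of internalizing symptoms, externalizing problems, social-occupational functioning and global adaptive functioning the primary outcomes. Statistical Methods estimates them by latent growth mixture modeling (aim 1) and carries class membership into aims 2 and 3. The aim 2 paragraph adds that analyses "will be performed on both complete cases and 5 imputed data sets".

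On expected loss, Sample Size and Power Analysis states: "Assuming a retention rate of 65% to reach an effective sample size of 780, we needed to recruit 1200 participants". Administrative Data lists service variables still to be extracted from military records: "Armed Forces Qualification Test score, training dates, and military discharge".

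**The concern.** A growth mixture model sorts people by the shape of their scores over time, so the within-person covariance across waves is the information it uses. Three features of the stated rule work against that.

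- **Later waves are unavailable.** Someone who misses time 2 but answers at times 3 and 4 receives a time 2 value that cannot reflect those later scores. Such returns are to be expected, because the survey procedures include contacting nonrespondents.
- **One population is assumed.** A regression fitted to all participants knows nothing of the classes. A recruit whose distress begins after training has earlier scores that look resilient, so the imputed value is drawn toward the majority. This affects most the new-onset class that aim 1 hypothesizes.
- **Pooling does not fit the target.** The usual combining rules average parameters that mean the same thing in every set. They do not apply to a number of classes, or to class labels that swap between the five sets.

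Trajectory shape and class size are at stake, and through class membership so are aims 2 and 3.

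**Working it through.** **The plan's own figures.** 780 / 0.65 = 1200, as stated. The power of 0.909 at n = 780 and 5 df is also reproduced, by a noncentral chi-square test of RMSEA 0.05 against 0.10. The value 0.10 is inferred from Table 4; the article gives only the null. Neither figure is affected by this point.

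**Correlation between adjacent waves.** Assume unit variances and a correlation of 0.60 between every pair of waves (the article gives none). Suppose time 2 is imputed from times 0 and 1 with a proper residual draw.

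1. Regression weight on each earlier wave: 0.6 / (1 + 0.6) = 0.375.
2. Correlation of an imputed time 2 value with an observed time 3 value: 2 × 0.375 × 0.6 = 0.45, against a true 0.60.
3. If a share p of participants miss time 2 and return at time 3, the overall correlation is (1 − p) × 0.60 + p × 0.45 = 0.60 − 0.15p.

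| Share missing time 2 and returning (assumed) | Time 2 to time 3 correlation |
|---|---|
| 0% | 0.600 |
| 5% | 0.593 |
| 10% | 0.585 |
| 35% | 0.548 (about 0.55) |

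The last row is an extreme. It needs the whole 35% of planned loss to be temporary, whereas the article's 35% is the complement of retention.

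**Simulation of the growth structure.** From the article: N = 1200, five waves, 65% observed at time 4. Assumed: random-intercept variance 0.6, residual variance 0.4, slope standard deviation 0.1 (slope variance 0.010), 88%, 80%, 72% and 65% observed at times 1 to 4, and gaps completely at random. There were 200 replicates per scenario.

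| Gaps and imputation model | Time 3 to time 4 correlation: imputed (full data) | Slope variance: imputed (full data) |
|---|---|---|
| Monotone, all earlier waves used | 0.638 (0.637) | 0.0104 (0.0099) |
| Monotone, baseline only | 0.528 (0.637) | 0.0027 (0.0099) |
| Monotone, no other wave used | 0.416 (0.637) | 0.0173 (0.0099) |
| Intermittent, all earlier waves used | 0.585 (0.642) | 0.0061 (0.0101) |

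The first row shows no material harm. The last shows slope variance down by 1 − 0.0061/0.0101 = 40% even when every earlier wave is used. That scenario is heavy: gaps are independent between waves, so 0.28 × 0.65 = 18% of participants miss time 3 and return at time 4.

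**Number of imputations.** Relative efficiency is 1 / (1 + f/m). At f = 0.35 and m = 5 it is 1 / 1.07 = 0.935, so five sets cost little for point estimates.

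**The case against.** The strongest reply is that the size of the harm is not established. The planned 35% is loss to follow-up, and people who leave for good have no later scores to be left out. With monotone dropout and all earlier waves as predictors, the correlations are preserved. No sentence restricts predictors to the current wave, and linear regression is given only as one example of an imputation method. All of this stands, and it makes the attenuation conditional. It does not remove the problem: a model identified at the end of a wave has no later data to draw on, the use of earlier waves is not stated, and pooling of class solutions remains unsolved.

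A second reply is that auxiliary variables and sensitivity analyses are often left to a fuller plan. That also stands, so their absence from the article is not the finding. The finding is the wave-by-wave rule that the article does state.

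Third, full-information likelihood also assumes missingness at random given the variables in the model. True; that is the reason for the added sensitivity analysis.

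Three stronger readings are tempting and unsupported:

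- **That the team already holds discharge records and ignores them.** Extraction is described in the future tense, and the limitations text reports permission only. What is in place is verification of training exposure and monitoring for discharge. Training failure and discharge are unnamed as predictors, which are left open; they are not excluded.
- **That a fifth of this cohort is expected to go missing through training failure.** The sentence "A considerable percentage (approximately 20%) of National Guard recruits fail to complete BCT" is a background rate. Follow-up depends on exposure to training, not completion, so exposed non-completers remain eligible.
- **That neither analysis is primary.** The missing-data section makes the combined imputed results the basis; the parallel complete-case run appears in the aim 2 paragraph.

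**Conclusion.** The point holds in a conditional form. The stated rule does not match a primary outcome that depends on all five waves jointly. The mismatch with class enumeration and pooling is structural and does not depend on the amount of missing data. The loss of correlation and slope variance does: it ranges from negligible (monotone dropout, all earlier waves used) to a time 2 to time 3 correlation of about 0.55 instead of 0.60 (all 35% missing and returning), with 0.585 to 0.593 for return shares of 10% to 5%. These figures rest on an assumed correlation of 0.60; the slope results rest on the assumed variances and completion rates listed above. The article gives no rate of intermittent nonresponse, so no single figure can be defended. The change is worth making because trajectories and classes carry every aim and the alternative is standard and inexpensive.

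**What to change.** 1. Fit the aim 1 mixture models by full-information maximum likelihood on all participants exposed to basic combat training with any wave observed, and name this the primary analysis. Include training completion and discharge status as auxiliary variables once they have been extracted from military records.
2. Impute missing predictors once, jointly across all waves, after data collection closes. Outcomes are then not imputed, so the number of classes and their labels can be carried from a single aim 1 solution.
3. Keep complete-case analysis as a sensitivity analysis, and add one in which unobserved scores after discharge are shifted toward worse functioning.
4. More than five imputations is optional.

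The cost is revised analysis text, some extra analysis work and computing time. Beyond the record extraction already planned, no new data are needed.
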